#### Study procedure

*Baseline assessment*. Basic demographic and treatment information will be collected through an electronic medical record system. Our study will gather self-reported demographic information, including age, sex, marital status, education level, etc. We will obtain surgery and treatment information, including surgery date, surgery type (axillary lymph node dissection or sentinel lymph node dissection), the total number of dissected lymph nodes, chemotherapy regimen, radiotherapy regimen, and cycle number of treatment (chemotherapy/radiotherapy).

*Ongoing assessment*. Table 1 shows the standard assessment process of the follow-up assessment of our study. Clinical evaluations will include evaluations of BCRL, RBC, and depression. At each follow-up visit, patients will receive an upper-limb volume assessment and physical and imaging examination [16]. The research nurse will help them complete the Beck Depression Inventory-II questionnaire about patients’ mental status.

**Table 1 pone.0285772.t001:** The standard assessment process in cohort study—time points and primary outcomes.

Time point	BMI	Patients with secondary lymphedema or not	Patients with oncology recurrence or not	Beck Depression Inventory II	Medicine cost

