**Chemotherapy therapy stage**	
Time points information	the number of chemotherapy cycles
Main information	body mass index(BMI), arm volume measurement (secondary lymphedema), assessment of tumor recurrence, scale results of Beck Depression Inventory-II
Financial information	treatment related cost

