### Statistical analyses

The following primary factors will be calculated when each of the study stages (perioperative stage, chemotherapy therapy stage, radiation therapy stage, follow-up stage) is completed: BCRL incidence, RBC rate, and incidence of depression. To calculate the incidence of the primary outcomes, we will sum the total of participants within each of the stages as the denominator and sum the total of people with one of the primary outcomes as the numerator. For every statistical analysis, the participants will be classified into two groups based on whether they developed secondary lymphedema. Incidence rates of breast cancer recurrence and depression will be calculated separately for groups. The chi-square test will be used to compare the rates rate between the two groups [26]. As a secondary outcome, depression symptoms will be repeatedly measured in this study. The results of the assessment of depression symptoms will be compared across periods and between treatment-related events using statistical analysis with repeated measures analysis of variance (ANOVA).

We will identify clinicopathological factors, surgery information, lymph node management, breast cancer-related treatment, and body mass index(BMI) as risk factors due to their reported associations with secondary lymphedema, recurrence of breast cancer, and depression symptoms. Multivariate logistic regression will be used to determine whether secondary lymphedema and other parameters can predict breast cancer recurrence. To assess the correlates with these risk factors and outcomes, we will describe the strength of the association using clinically meaningful and statistically significant effect sizes, and a correction will be based on demographic characteristics.

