### Missing data

We will assess missing data and record the study stage and reasons for missing data. Data in the previous stage will be retained and calculated if patients are lost to follow-up at this stage of the study. Missing data will not be handled using estimation.

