## Limitations

Data from breast cancer patients will only be collected from a large district general hospital. It is difficult to put the scheme of further multicentric trials into practice under the normalization of epidemic prevention and control. Moreover, similar to other cohort studies, the situation in which breast cancer survivors are lost to follow-up seems inevitable. The completeness of treatment and follow-up data will be important to assess the correlation between breast cancer-related lymphedema and recurrence and disease burden (depression and medicine cost). Loss of follow-up will continue to hinder the data completeness of our cohort study.

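### Repeated-measures ANOVA for BDI-II, with no estimation of missing data, deletes women lost before a later period together with their earlier scores, against the protocol's own retention rule

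*Protocol article*

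**What the plan says.** The Statistical analyses section gives depression its role and its method. "As a secondary outcome, depression symptoms will be repeatedly measured in this study", and the scores are to be set against each other by period and by treatment-related event "using statistical analysis with repeated measures analysis of variance (ANOVA". The same section groups women, for every analysis, by whether they developed secondary lymphedema. It names no mixed model, no generalised estimating equations and no rule for women with different numbers of chemotherapy cycles.

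The Missing data section holds two sentences that matter here. One is "Data in the previous stage will be retained and calculated if patients are lost to follow-up at this stage of the study". The other is "Missing data will not be handled using estimation".

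The schedule comes from Table 1 and the stage descriptions. BDI-II is taken before surgery, at each chemotherapy cycle up to an unspecified last one, before and after radiotherapy, and at ten follow-up visits from month 9 to month 36. Under Study procedure, for each follow-up visit, "The research nurse will help them complete the Beck Depression Inventory-II questionnaire about patients’ mental status". Table 2 records "the number of chemotherapy cycles" as a variable, so the count is treated as differing between women.

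Loss is expected. Sample size calculation assumes 10% dropout, and Limitations states "Loss of follow-up will continue to hinder the data completeness of our cohort study".

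**The concern.** Classical repeated-measures ANOVA needs a value for every woman at every level of the within-subject factor. If nothing may be filled in, a woman with an empty cell leaves the analysis, and all her recorded scores go with her. The method and the missing-data rule together therefore give a complete-case analysis, in a cohort that expects loss over three years.

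Two things are at stake. First, the named method cannot deliver the protocol's rule that data from earlier stages stay in use for women lost later. Second, the depression trajectory would describe only women who stayed. If women who are more depressed, more ill or recurring are likelier to be lost, that trajectory looks better than the cohort's true course. This direction is plausible, but the protocol gives no data on it and it remains an assumption.

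**Working it through.** **The protocol's own figure.** The only computed number is the target of 1557, which concerns lymphedema and recurrence incidence. With p = 0.1757, d = 0.02 and z = 1.96 (two-sided 5%, assumed because none is stated), N = 1.96² × 0.1757 × 0.8243 / 0.02² = 1391. Allowing for 10% dropout, 1391 / 0.9 = 1546, close to 1557 but not exact. BDI-II plays no part in it. The use made of 1557 below is 1557 × 0.9 = 1401 women without dropout and about 156 with dropout.

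**Number of occasions (Table 1).** 1 + n + 2 + 10 = 13 + n. The protocol gives no range for n. Assuming n = 4 to 8, the count k is 17 to 21.

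**Method against retention rule.** Take a woman lost after radiotherapy, before any follow-up visit.
- Missing data section: her perioperative, chemotherapy and radiotherapy scores are kept and used.
- Statistical analyses section: her follow-up cell is empty and may not be filled, so ANOVA omits her and those scores.

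The conflict arises whether the within-subject factor is the visit or the stage. Up to the planned 10% are affected.

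**Reading A: visit is the factor.** The complete share among women without dropout is (1 − m)^k, where m is an assumed missed-visit rate, equal and independent across visits. Counts are out of 1401.

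| m | k = 17 | k = 21 |
|---|---|---|
| 1% | 84% (1181) | 81% (1135) |
| 2% | 71% (994) | 65% (917) |
| 5% | 42% (586) | 34% (477) |

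The share of recorded scores discarded is 1 − (1 − m)^k / (1 − m), about 28–33% at m = 2% and 56–64% at m = 5%. Unequal cycle counts add cells that are empty by design: a woman with 4 cycles in a layout for 8 has 4 of 21 cells that could never be filled.

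**Reading B: stage is the factor, and available scores are averaged within stage.** A woman without dropout has all four values with probability (1 − m)(1 − mⁿ)(1 − m²)(1 − m¹⁰). This is 98% at m = 2% and 95% at m = 5%, the same to the nearest percent for n = 4 and n = 8. Single missed visits and cycle counts then matter little. Women lost before a stage are still removed.

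**Lymphedema grouping.** Table 1 assesses lymphedema at every visit after surgery, so status can change during the study. A fixed split by whether a woman ever developed it attributes her scores before onset to the lymphedema group, under either reading.

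**The case against.** The strongest reply is that the protocol nowhere makes visit the within-subject factor. It compares scores across *periods*. The Discussion uses that word for perioperative, treatment and follow-up, and the Statistical analyses section is organised by the four stages. A reader might infer that every woman with one missed visit is dropped, that differing cycle numbers cannot be handled, or that only about a third to a half of the cohort would be analysed (for example 0.9 × 0.97^19 = 50% and 0.9 × 0.95^21 = 31%). The arithmetic is right, but the documents do not support these as statements of fact. They need Reading A, an assumed cycle count, and independent misses at one assumed rate. Misses that cluster within women would leave more women complete. Chemotherapy assessments take place on the ward at each cycle, and reminders are planned, so low rates are possible. This part of the reply stands, and it confines the visit-level figures to a scenario.

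It does not remove the conflict with the retention rule. The protocol does not state the within-stage averaging on which Reading B relies. That averaging would also merge ten visits from month 9 to month 36 into one value, and women lost before a stage would still be deleted.

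A second reply is that such detail belongs in an analysis plan that is not shown. That is fair for the covariance structure. But the protocol itself fixes both the method and the missing-data rule, and those two are what clash.

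Third, Study sample excludes women who could not complete all treatment and three-year follow-up. If that is applied after enrolment, selection also arises there, and no change of model recovers those women.

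**Conclusion.** The point holds in a limited form. Repeated-measures ANOVA with no estimation of missing data is a complete-case analysis. It contradicts the protocol's rule that earlier-stage data of women lost later are retained and used, for up to the planned 10% of the cohort (about 156 of 1557), whichever time factor is meant.

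Any larger loss depends on a choice the protocol leaves open. With visit as the factor, 65–71% of women without dropout would be complete at 2% missed per visit and 34–42% at 5%, assuming 4 to 8 cycles and independent misses. With stage averages, 95–98% would be.

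Bias towards women who are well is plausible but assumed. The point concerns a secondary outcome in a study that describes itself as explorative, and it does not touch the target of 1557. The change should be made, but the primary outcomes do not depend on it.

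**What to change.** In Statistical analyses, replace repeated-measures ANOVA for BDI-II with a linear mixed model on all recorded scores, specified as follows:

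- **Time factor:** name it, either stage or months since surgery.
- **Pre-surgery score:** keep it as the first outcome occasion. It is the only perioperative measurement, so making it a covariate would take that period out of the planned comparison.
- **Within-woman correlation:** a subject random effect or a suitable within-subject covariance.
- **Lymphedema and recurrence:** time-varying covariates, so that scores before onset are not attributed to the lymphedema group.

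In Missing data, add a sentence saying that this model imputes no values, is consistent with both existing sentences of that section, and is valid under missing at random. The no-estimation rule need not be withdrawn. Add one sensitivity analysis for informative dropout.

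The cost is a change of wording and slightly more analysis work in routine software, with no extra data or recruitment. The price is reliance on missing at random, which the sensitivity analysis is there to probe.

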## Abstract

**Introduction:**

The primary aim is to determine the factors associated with breast cancer-related lymphedema and to identify new associated factors for the recurrence of breast cancer and depression. The secondary objective is to investigate the incidence of breast cancer-related events (breast cancer-related lymphedema, recurrence of breast cancer, and depression). Finally, we want to explore and validate the complex relationship among multiple factors influencing breast cancer complications and breast cancer recurrence.

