## Introduction

Breast cancer-related lymphedema (BCRL) is closely related to a high risk of cancer-related treatment, breast cancer recurrence, and disability [1]. In breast cancer patients, secondary lymphedema is a symptom cluster encompassing progressive upper-limb swelling, skin changes, limb numbness, pain and discomfort, restricted range of motion, and nonpitting edema [2]. These would decrease physical and mental function, increase disease burden and increase financial costs. It is a common complication in breast cancer patients [3–6]. Considering the establishment of a baseline of the upper limb and tracking changes, a screening cohort of secondary lymphedema may be the optimal solution to develop screening programs and evaluate the prevalence of breast cancer-related lymphedema in China.

Breast cancer recurrence (BCR) is a negative outcome in patients with breast cancer after either mastectomy or breast-conserving therapy (BCT) [7]. Breast cancer can recur locally, regionally, and/or at distant metastatic sites [8]. It is a hammer blow for breast cancer survivors [9]. It directly threatens breast cancer survivors’ life expectancy and decreases their quality of life. BCRL and BCR share risk factors such as higher BMI, pathological type, breast cancer location, tumor node metastasis(TNM) staging and comorbidities, and treatment-related factors (surgery, radiotherapy, and chemotherapy) [10]. Early detection helps implement personal and precise medical precautions for patients with secondary lymphedema (or breast cancer recurrence).

Up to 30% of breast cancer survivors have depressive symptoms [11]. Depressive affect includes emotional lability, irritability, and social withdrawal [12]. Depression is an emotional difficulty associated with an increased disease burden and treatment-related cost and a decreased ability to cope with breast cancer. Fear of cancer recurrence also directly affects mental health, especially anxiety and depression [13].

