## Patients and methods

This study is a prospective cohort study of breast cancer survivors. This study aimed to investigate and evaluate the incidence and correlation of BCRL, BCR, and depression. The primary outcome measures include the incidence and correlation of BCRL and BCR within three years. Choice of the time frame because three years is a high-incidence period of BCRL and BCR. The secondary outcome is depression.

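### No multivariable model is named with lymphedema as outcome, and the only correction stated for the risk-factor associations is demographic, so estimates for the first-named aim are open to confounding and selective emphasis

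*Protocol article*

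**What the plan says.** The abstract opens with the aim: "The primary aim is to determine the factors associated with breast cancer-related lymphedema". It goes on to new factors for recurrence and depression. Patients and methods then states: "The primary outcome measures include the incidence and correlation of BCRL and BCR within three years".

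The Statistical analyses section sets out the following.

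- Role of lymphedema: "For every statistical analysis, the participants will be classified into two groups based on whether they developed secondary lymphedema". Recurrence and depression rates are compared between these groups by chi-square.
- Candidate factors: "We will identify clinicopathological factors, surgery information, lymph node management, breast cancer-related treatment, and body mass index(BMI) as risk factors". The same sentence links them to lymphedema, recurrence and depression.
- The one multivariable model: "Multivariate logistic regression will be used to determine whether secondary lymphedema and other parameters can predict breast cancer recurrence".
- Description of associations: "we will describe the strength of the association using clinically meaningful and statistically significant effect sizes". The sentence ends with the adjustment: "a correction will be based on demographic characteristics".

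The Introduction says: "BCRL and BCR share risk factors such as higher BMI, pathological type, breast cancer location, tumor node metastasis(TNM) staging and comorbidities". It adds surgery, radiotherapy and chemotherapy to that list.

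**The concern.** Three statements do not fit the aim or the article's own account of the disease.

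1. **Outcome.** Factors for BCRL come first in the aim, but the named model has recurrence on the left-hand side and lymphedema among the predictors. Lymphedema otherwise appears as an incidence and as the grouping variable. No named model enters the BCRL factors together.
2. **Adjustment.** Stage, nodal surgery, number of nodes removed and radiotherapy details are likely to be correlated. A demographic correction cannot separate them. The chi-square of recurrence by lymphedema group has no adjustment at all.
3. **Reporting.** If statistical significance decides which effects are described, the described effects are too large on average.

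The Discussion intends the results to inform an early-screening package. A factor that only stands in for another, or whose effect is inflated, could then shape who is screened.

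**Working it through.** **Event numbers (can the data carry the model?)**

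Inputs from Sample size calculation: BCRL 17.57%, recurrence 15.53%, permissible error 2%, dropout 10%, N = 1557. Assumed: two-sided alpha 0.05, so z = 1.96.

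- Plan's figure: N = z²p(1−p)/d² = 1.96² × 0.1757 × 0.8243 / 0.02² = 1390.9, rounded up to 1391. Then 1391 / 0.90 = 1546, which is 0.7% below the stated 1557. The BCRL rate drives N.
- Completers: 1557 × 0.90 = 1401.
- BCRL events: 1401 × 0.1757 = 246. Recurrence events: 1401 × 0.1553 = 218.
- With about 20 parameters this is 246/20 = 12.3 and 218/20 = 10.9 events per parameter. Event numbers do not stand in the way of a BCRL model.

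**Confounding among BCRL factors (illustration)**

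Assumptions, none from the document: a binary factor X with no effect on BCRL, a binary clinical confounder C, both at 50%, overall BCRL 17.57%, 700 women per level of X. With r = √OR(X,C), P(C | X=1) = r/(1+r) and P(C | X=0) = 1/(1+r).

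Worked case, OR(X,C) = 2 and OR(C,BCRL) = 3:

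- P(C | X) = 0.586 and 0.414. BCRL risk is 0.1005 without C and 0.2509 with C.
- Risk with X: 0.586 × 0.2509 + 0.414 × 0.1005 = 0.189. Risk without X: 0.414 × 0.2509 + 0.586 × 0.1005 = 0.163.
- Odds ratio not adjusted for C: 1.20, significant in 24% of studies.

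| OR(X,C) | OR(C,BCRL) | OR for X, true value 1 | Significant |
|---|---|---|---|
| 1.5 | 2 | 1.07 | 7% |
| 2 | 3 | 1.20 | 24% |
| 3 | 3 | 1.32 | 51% |
| 4 | 4 | 1.53 | 85% |

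**Confounding of the chi-square (illustration)**

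Assumptions: 40% of women are high stage, lymphedema and recurrence are independent within stage, and the overall rates are held at 17.57% and 15.53%.

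- Moderate gradient (BCRL 25% vs 12.6%, recurrence 25% vs 9.2%): P(both) = 0.4 × 0.25 × 0.25 + 0.6 × 0.1262 × 0.0922 = 0.0320. Recurrence is 0.0320/0.1757 = 18.2% with lymphedema and (0.1553 − 0.0320)/0.8243 = 15.0% without. Odds ratio 1.26 (1.27 if the rounded stratum rates are used).
- Steeper gradient (28% vs 10.6%, 28% vs 7.2%): P(both) = 0.0360, recurrence 20.5% vs 14.5%, odds ratio 1.52.
- With 246 vs 1155 women the chi-square is significant in about 26% and 64% of studies, against a nominal 5%.

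In this set-up, putting stage in the model removes the bias.

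**Describing only significant results (illustration)**

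200,000 simulated studies, 700 vs 700 women, overall BCRL 17.57%:

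| True OR | Significant | Mean OR among the significant |
|---|---|---|
| 1.1 | 10% | 1.37 |
| 1.2 | 25% | 1.43 |
| 1.3 | 46% | 1.47 |
| 1.5 | 82% | 1.57 |
| 2.0 | 99.8% | 2.01 |

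The inflation matters for modest effects and vanishes for large ones.

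**The case against.** The strongest reply is that the section plans more than its wording shows. Several parts of it stand.

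- A reader might infer that all associations are adjusted for demographics alone. The text does not say so. The recurrence model takes other parameters beside lymphedema, and the clinical, surgical and treatment factors listed just before it are the natural candidates. BMI is itself listed under demographic data in the perioperative-stage section and in Table 2.
- A reader might infer that non-significant results will be withheld. The text does not say that either. It couples significance with clinical meaning and may be no more than loose wording.
- The grouping of every analysis by lymphedema cannot be literal, because BCRL incidence is itself calculated. The section also plans to relate the risk factors to the outcomes, with lymphedema among them. So some demographically corrected BCRL association is planned, but its model is not named.
- The aim also covers recurrence and depression, so the recurrence model answers part of it.
- Study sample recruits women due for mastectomy, chemotherapy and radiotherapy. Receipt of treatment therefore varies little, and it is mainly extent and regimen that can confound.
- The odds ratios of 1.26 and 1.52 belong to the crude comparison and not to a recurrence model that includes stage.
- A full covariate list is commonly left to an analysis plan.

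These replies limit the point without removing it. The section does choose an outcome for its named multivariable model and does state an adjustment set for the associations. Neither choice matches the first-named aim or the shared risk factors in the Introduction.

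**Conclusion.** The point holds as a mismatch between aim and stated analysis. A multivariable model is named for recurrence and none for BCRL, the one correction stated for the risk-factor associations is demographic, and their description is tied to significance. Followed as written, the BCRL estimates are open to confounding by one another and to selective emphasis, and the chi-square of recurrence by lymphedema group can only be descriptive.

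It would go too far to conclude that the primary aim will be answered with confounded and selectively reported estimates. That states a risk as a certainty. The size of any bias rests on assumed stratum rates and assumed associations between factors. The ranges above (1.07 to 1.53 for a null BCRL factor, 1.26 to 1.52 for the crude lymphedema-recurrence comparison) show what is plausible and are not predictions. The change should be made before analysis because it bears on the primary aim and costs little.

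**What to change.** 1. Add a multivariable model with 3-year BCRL as outcome. Logistic regression is enough. Enter TNM stage, pathological type, nodal surgery and number of nodes dissected, chemotherapy and radiotherapy details, comorbidities, BMI and demographics together.
2. State that the other parameters in the recurrence model include these same clinical and treatment factors. Base the lymphedema-recurrence conclusion on that model and label the chi-square comparison descriptive.
3. Report every prespecified factor with its estimate and 95% confidence interval, whatever its p-value, and drop significance as a criterion for describing an association.

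Cost: analysis wording only. The variables are already collected (Baseline assessment, the perioperative-stage section and Table 2). About 246 BCRL and 218 recurrence events support roughly 20 parameters at 10 or more events each. N is unchanged, because it rests on the precision of a proportion. The price is slightly wider intervals for adjusted estimates.
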